### Sample size/power calculation

The school is the unit of the study. The power/sample size calculation was performed using a test for two means in a cluster randomized design function implemented in PASS 12 [19]. A power calculation indicated that with 8 schools in each arm and 68 participants per cluster, the study would have 90% power (1-β) to detect an underlying medium standardized difference between the means (effect size) of 0.3 following the intervention, at a two-sided 5% significance level (α), assuming an intra-class correlation coefficient (ICC) of 0.05 or 5% [20, 21].

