### Participants and recruitment process

The participants of the study will include children in grade four (aged 9-11 years) and grade seven (aged 12-15 years), as well as parents/primary caregivers, Life Orientation (LO) educators, principals, members of the community, the latter through the school governing body (SGB). When the data has been collected meetings will be held with the SGBs (from whom permission will be required prior to the study) to inform them of the results and get their input on the way forward. They will also be the link with the wider community. Other stakeholders will include DoBE, DoH, Sports and Recreation, Health Promotion Coordinators, the District Nutrition Coordinator and School Health Teams in iLembe district, KwaZulu-Natal. The study setting will be primary schools in iLembe district.

A complete list of all schools with grade four and seven children in iLembe district will be provided by the Provincial Department of Basic Education. The list includes over 400 primary schools from which 16 schools will be selected randomly with probability proportional to size (PPS). There will be four schools from each of the four sub-districts, which will be randomly assigned into the two study arms (control *n* = 8, intervention n = 8). Two schools will receive the intervention and two schools will serve as controls in each of the four sub-districts. All children and adolescents in grade four and seven attending these schools and their parents/primary caregiver will be invited to participate in the study. Children and adolescents must provide assent in writing via the consent forms. Parents/caregiver must also provide consent for participation in the study for the children/adolescents and themselves (Additional file 2). South African schools are arranged into quintiles determined by the National Treasury, based on scores reflective of the poverty levels where a community is situated. The DoBE uses these poverty classifications that range from quintiles 1–5, where quintile five is the least poverty-stricken and one is the most poverty-challenged quintile, to classify schools. Most of the primary schools in iLembe district are from quintiles 1 and 2, hence it is important to understand the daily challenges these communities face regarding housing, socio-economic status, employment, as well as health outcomes as these are regarded as schools with low socio-economic status and exempt from school fees [18].

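### The stated 90% power does not follow from its own inputs: 8 schools per arm, 68 children per school, ICC 0.05 and an effect of 0.3 SD give about 60–66% for the unadjusted comparison described

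*Protocol article*

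**What the plan says.** The section on sample size and power names its method as "a test for two means in a cluster randomized design function implemented in PASS 12". It puts the design at "with 8 schools in each arm and 68 participants per cluster" and the clustering at "assuming an intra-class correlation coefficient (ICC) of 0.05 or 5" per cent. For a two-sided test at 5% of the difference after the intervention, it claims that "the study would have 90% power (1-β) to detect an underlying medium standardized difference between the means (effect size) of 0.3".

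The section on participants and recruitment confirms the number of clusters. Sixteen schools are drawn, four from each sub-district, and allocated 8 to 8: "Two schools will receive the intervention and two schools will serve as controls in each of the four sub-districts". The figure of 8 per arm is therefore not a misprint confined to one sentence.

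The power statement mentions no baseline covariate, no assumed correlation between baseline and end of study, and no other reduction in variance.

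**The concern.** With few clusters and an ICC of 0.05, the number of schools governs the precision, and adding children to each school helps little. Eight schools per arm is few for an effect of 0.3 SD, so 90% looked too high.

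This paragraph is the article's only justification for the size of the trial. If the power of the comparison it describes is nearer 60%, a true effect of 0.3 SD would be missed by that comparison in 34–40% of trials rather than 10%. A null result read against a claimed 90% would then be taken as stronger evidence against such an effect than the described design can give. The Discussion ties roll-out to further schools, including the control schools, to whether the programme proves effective, so the misreading could matter in practice.

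**Working it through.** **Inputs** (all from the sample size section; schools per arm confirmed under participants and recruitment): k = 8 schools per arm, m = 68 children per school, ICC = 0.05, standardized effect d = 0.3, two-sided α = 0.05. Stated power: 90%.

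**Trying to reproduce the stated figure**

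1. Design effect = 1 + (m − 1) × ICC = 1 + 67 × 0.05 = 4.35.
2. Children per arm = 8 × 68 = 544. Effective number per arm = 544 / 4.35 = 125.06.
3. Standard error of the standardized difference = √(2 / 125.06) = 0.1265.
4. Effect over standard error = 0.3 / 0.1265 = 2.37.
5. Normal approximation: Φ(2.37 − 1.96) = Φ(0.41) = 66.0%.
6. Noncentral t with 2 × (8 − 1) = 14 degrees of freedom: 59.8%. Using child-level degrees of freedom (1,086) instead gives 65.9%.

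The stated 90% is not reproduced. The shortfall is 24 points (normal) to 30 points (t).

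**Other readings of the same inputs**

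| Variant | Normal | t |
|---|---|---|
| As stated | 66.0% | 59.8% (14 df) |
| Allowing for four sub-districts | – | 58.0% (11 df) |
| One-sided 5% | 76.7% | 72.9% |
| 68 per grade, so 136 per school | 71.0% | 64.8% |
| Unlimited children per school | 76.5% | 70.4% |
| Clustering ignored | 99.9% | – |

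The fifth row is the ceiling. As m grows, the variance of the difference falls only to 2 × 0.05 / 8 = 0.0125, so the standard error cannot go below 0.1118 and 0.3 / 0.1118 = 2.68. Inviting every Grade 4 and Grade 7 learner therefore cannot bring the unadjusted comparison to 90%.

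**What would give 90%, changing one input at a time**

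- Effect: 0.41 SD (normal) or 0.44 SD (t).
- ICC: about 0.020 (normal) or 0.015 (t).
- Schools per arm, at 68 each: 15 (normal, 90.1%) or 16 (t with 30 df, 90.1%).

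**Baseline adjustment** (every correlation here is an assumption; the article gives none)

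With correlation r_s at school level and r_c at child level, the variance of the difference is (2/8) × [0.05 × (1 − r_s²) + (0.95/68) × (1 − r_c²)]. The t column uses 13 df, one being spent on the covariate.

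| School level r_s | Child level r_c | Normal | t |
|---|---|---|---|
| 0.5 | 0.5 | 78% | 72% |
| 0.7 | 0.7 | 91% | 87% |
| 0.8 | 0.8 | 98% | 95% |
| 0.5 | 0.8 | 83% | 77% |

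The school-level correlation matters most. Of the unadjusted bracket, 0.05 + 0.95/68 = 0.0640, the school part is 0.05, or 78%.

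**The case against.** The strongest reply is that the trial may not be analysed as a plain end-of-study comparison. Baseline BMI Z scores are collected, and the planned statistical analysis lists change in BMI as an outcome and describes mixed models comparing the periods before and after the intervention. Such an analysis could well have more power than 60–66%.

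Part of this stands. The 34–40% risk of missing the effect, and the ceiling on power, belong to the unadjusted comparison at ICC 0.05. They are not properties of whatever analysis is finally run, whose power cannot be worked out from the article. But the reply does not rescue the stated figure. The power paragraph describes a two-means calculation with no covariate and no correlation, and an unstated correlation cannot make it correct.

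Two stronger readings are tempting, and the document supports neither.

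- A reader might infer that, because baseline values are available, adjustment restores 90% and no more schools are needed. That holds only for favourable correlations at both levels. At 0.7 the t-based power is still 87%, and with 0.8 among children but 0.5 among schools it is 77%.
- A reader might infer how the error arose. Sixteen schools per arm would give 90.1% by the t test, so the total of 16 could have been taken for the number per arm; an ICC nearer 0.02 or 0.015 would also give about 90%. Both are conjecture. Nothing in the article shows which entry was misreported.

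**Conclusion.** The power statement is wrong as written. For the unadjusted two-means cluster comparison it describes, the stated inputs give about 66% (normal) or 60% (t, 14 df) against 90% claimed. At that ICC and effect, no cluster size reaches 90% with 8 schools per arm.

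This rests only on figures in the article and on equal school sizes, which is how the article states them. It needs no outside value. The gap is far larger than any difference between formulas or rounding could produce. Whether a baseline-adjusted analysis would reach 90% is open: over the correlations tabulated it runs from 72% to 98%.

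**What to change.** Rerun the calculation and reconcile the number of schools, the ICC, the effect size and the power, since the article does not show which of them is misreported. Then take one of two routes.

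- **If the inputs stand:** state that 8 schools per arm, 68 children per school and ICC 0.05 give about 60% power (t, 14 df) for 0.3 SD, and 90% only for about 0.44 SD (0.41 SD by the normal approximation).
- **If power is to rest on a baseline-adjusted analysis:** say so, state the assumed correlations between baseline and end of study at child level and at school level, and show power over a range of both. Unless those correlations can be justified, do not claim that the present number of schools is enough.

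The text change is one paragraph. The cost is larger if the rerun confirms about 60%, because the sponsor must then accept a lower power or a larger detectable effect, justify the adjusted basis, or reconsider the number of schools.

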### Randomization

The school is the unit of the study. A biostatistician who does not have direct contact with study participants will generate the random allocation sequences using a computerized random number generator. After the inclusion of each cluster, the allocation of that particular cluster will be provided to the study coordinator. There will be no crossover between study arms.

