Anthropometry	Weight and height for all participating children and adolescents	Phase 2- Intervention phase	Weight and height will be measured using a digital weighing scale, and stadiometers. (Model no. 210/217/876; Seca, Hamburg, Germany). The weight of the participant will be taken to the nearest 0.1 kg for accuracy. The participants will be weighed with minimal clothing, and preferably with an empty bladder and before a meal [26]. Measurements using the stadiometer will be taken to the nearest 0.1 cm for accuracy. The participants will be measured without shoes. Participants are required to stand with their legs straight, heels and the height measure touching at the back, arms at the sides, relaxed shoulders, with chin level to ground and looking straight ahead [26]. Weight and height measurements will be taken in duplicate for accuracy and a correct average. The body mass index (BMI) for age Z scores, according to the 2006 WHO Growth Standards for children, will be used to classify being at risk of overweight with a Z score of SD 1, overweight with a Z score SD > 1 and obese as a Z score SD > 2 [27].
Workshop	LO educators	Phase 2- Intervention phase	To facilitate study implementation, educators will be invited to attend a two-day training workshop at the university to assist educators in understanding and delivering the classroom lessons as part of the intervention. They will also be provided with the findings of the baseline data to assist them.

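### A school's arm is released when the school is included, and nothing in the article holds it back until consent and baseline measurement are complete

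*Protocol article*

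**What the plan says.** In the protocol article, the Randomization section separates generation of the sequence from field contact: "A biostatistician who does not have direct contact with study participants will generate the random allocation sequences using a computerized random number generator". It then fixes the release rule: "After the inclusion of each cluster, the allocation of that particular cluster will be provided to the study coordinator". The same section and the sample size section both name the school as the unit.

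Under Participants and recruitment process, four schools are taken from each of four sub-districts, and the split is exact: "Two schools will receive the intervention and two schools will serve as controls in each of the four sub-districts". Recruitment within a school is by open invitation: "All children and adolescents in grade four and seven attending these schools and their parents/primary caregiver will be invited to participate in the study". Enrolment is opt-in. Learners give written assent and, in addition, "Parents/caregiver must also provide consent for participation in the study for the children/adolescents and themselves".

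The Abstract dates baseline to March 2020 without linking it to allocation. Under Study components and implementation, baseline questionnaires go to learners, Life Orientation educators and parents in phase 2, after the qualitative phase 1 work in the schools. Table 1 places weight and height in phase 2 as well. Its Workshop row says of the educators: "They will also be provided with the findings of the baseline data to assist them".

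**The concern.** Randomising schools gives comparable groups of children only if the children who enrol, and the baseline data they supply, do not depend on the arm. In a cluster trial with individual consent, that protection is lost if the people running recruitment already know the arm. Effort in chasing consent forms may differ, families may respond differently to a school that is to receive a programme, and learners, parents and educators may answer baseline questions on diet and activity with the programme in mind.

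The release rule here is triggered by inclusion of the cluster, not by completion of consent or baseline. If inclusion means the school's entry, the coordinator holds the arm while assent, consent, weighing and questionnaires are still to come, possibly for the whole of phase 1 as well. At stake is the comparability of the enrolled children, and the baseline values against which change in the self-reported secondary outcomes is judged.

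**Working it through.** The plan gives no figure on this point, so there is none to reproduce. The check has three parts.

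**1. Order of events**

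| Step | What the article fixes | Tied to allocation? |
|---|---|---|
| School's entry | Governing-body permission needed before the study; schools drawn from a departmental list | Trigger for release, if this is what inclusion means |
| Release of arm | On inclusion of that school, to the coordinator | – |
| Assent and parental consent | Required; no date | No |
| Baseline questionnaires and anthropometry | Phase 2, March 2020 | No |
| Educator workshop | Uses baseline findings, so after baseline | No |

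Inclusion is not defined, and there are two readings. If it means the school's entry, both consent and baseline are open to knowledge of the arm. If it means that the school's learners and parents have been enrolled, consent is protected, but baseline measurement still is not. On neither reading does the text hold release back until baseline is complete.

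**2. Predictability of allocations (secondary)**

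Inputs: four schools per sub-district, two per arm, four sub-districts (Participants and recruitment process). Assumptions: schools in a sub-district are included one at a time, each arm is disclosed before the next school enters, and the 2:2 split is known to the coordinator.

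The six equally likely orders are IICC, CCII, ICIC, ICCI, CICI and CIIC. In the first two, the third and fourth arms are both certain in advance (2 each). In the other four, only the fourth is certain (1 each).

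- Expected per sub-district: (2 × 2 + 4 × 1) / 6 = 8/6 = 1.33 of 4
- All four sub-districts: 4 × 1.33 = 5.33 of 16, or 33.3%
- Range: 4 × 1 = 4 to 4 × 2 = 8 of 16

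If a sub-district's four arms are released together after consent and baseline, the number deducible in advance is 0.

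**3. Would the planned baseline comparison reveal a problem?**

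The statistical analysis section will look for significant baseline differences between arms. Inputs from the sample size section: 8 schools per arm, 68 learners per school, ICC 0.05. Assumption: the same ICC applies to the baseline variable.

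- Design effect: 1 + (68 − 1) × 0.05 = 4.35
- Learners per arm: 8 × 68 = 544
- Standard error of the arm difference: √(2 × 4.35 / 544) = 0.126 SD
- Observed difference needed for two-sided 5% significance (normal approximation): 1.96 × 0.126 ≈ 0.25 SD

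A true imbalance of 0.25 SD would be flagged only about half the time, and smaller ones less often. For scale, the effect the trial is designed to detect is 0.3 SD. A non-significant baseline test is therefore weak reassurance.

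**The case against.** **The order is not stated.** A reader might infer that arms are disclosed before families consent and before baseline. No section says so. The only inclusion criteria in the article concern learners and parents, which leaves room for the reading that a school is included once its participants are enrolled. This stands, and it limits the point to the absence of a safeguard.

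**The article is a condensed text.** The study-design figure, the SPIRIT checklist and the consent file are not visible here, and any of them might give the sequence. This stands in part. But the article does not leave the matter open: it states a release rule with a trigger, and the trigger is the wrong one to rely on unless inclusion is defined to cover consent and baseline.

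**Only the coordinator is told.** The text does not say that fieldworkers, schools or families learn the arm at that moment. The risk therefore assumes that the coordinator influences recruitment or passes the information on. Nothing in the article rules this out.

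**Predictability has little to act on.** A reader might take the one-third figure as a serious flaw. Schools are drawn with probability proportional to size and every learner in the two grades is invited, so the coordinator has no stated choice over who enters. Knowing the next arm could matter only through the order, refusal or replacement of schools, on which the article is silent. This objection largely stands.

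**BMI is partly protected.** Weight and height are measured by instrument, in duplicate, and the analysis lists change in BMI. A stable difference in baseline level would largely cancel in a change analysis. A reader might nonetheless infer a bias of known size in the primary comparison. The documents give no consent rates and no differences between consenters and refusers, so no size can be supported. What does not cancel is selection on characteristics that predict change, or baseline self-report altered by knowing the arm.

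**Conclusion.** The concern holds as a weakness in a stated rule. Release of the arm is tied to inclusion of the school, and nothing shown delays it until opt-in consent and baseline measurement are complete. Consent and baseline responses could therefore differ by arm, with the self-reported secondary outcomes more exposed than measured BMI. The planned significance check at baseline would miss most imbalances below about 0.25 SD.

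This rests on reading inclusion as the school's entry. On the alternative reading the gap narrows to baseline measurement, and the sentence still needs to say so. The size of any bias is unknown. The 5.3 of 16 deducible allocations is correct under its assumptions but secondary. The matter should be corrected because the remedy is cheap and bias of this kind is hard to undo in analysis.

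**What to change.** Replace the release sentence in the Randomization section. The new text should say that the biostatistician discloses allocations only after learner assent, parental consent, anthropometry and all baseline questionnaires are complete, preferably for the four schools of a sub-district together. It should also define inclusion of a cluster. Joint release removes the predictability issue at the same time, and planned numbers do not change.

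The cost is small but not nil. Intervention schools learn their arm later. The workshop timing also needs attention: the Workshop row of Table 1 implies that baseline comes first, since educators receive its findings, while the Health Promotion Toolkit row puts the workshops before the study starts. These two statements must be reconciled with each other and with the new order before one can say that nothing is delayed.

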### Inclusion/exclusion criteria

The inclusion criteria include: a) Children and adolescents in grades four and seven (aged 9–15 years). b) Parent/primary caregiver of the participating children/adolescents. c) Children and adolescents with physical disabilities will be included in the study but excluded from the anthropometry.

### Study components and implementation

The study will consist of two phases: Phase 1 is a baseline elicitation phase using a qualitative paradigm, whereby the formative assessment will inform the development of the intervention for use in phase 2. A thorough search and review of available scientific literature will be carried out to determine what is currently being done regarding learners, particularly in respect to health promotion concerning physical activity and dietary habits of school-going learners in South Africa and specifically in iLembe district, KwaZulu-Natal. During the elicitation phase focus group discussions (FGDs) will be conducted with selected members of the SGB, as well as selected children and adolescents in grades four and seven to explore current practices at each school. In-depth interviews will be conducted with principals regarding nutrition and PA at school. Based on the information obtained from the elicitation research phase, a plan for the intervention phase based on the Social Cognitive Theory (SCT) framework [22] will be developed and implemented. During the intervention phase structured questionnaires will be given to the children and adolescents in grades four and seven, the LO educators and the parents/primary caregivers of the participating children and adolescents to determine their understanding, knowledge, attitudes and behaviours regarding diet and physical activity at baseline and at the end of the study.

### Training

Fieldworkers will be recruited for the study and training will continue in 2020. A training manual will be compiled by the principal investigator and co-investigators of the study, who will also facilitate the training. During the training fieldworkers will be given an in-depth background about the significance of the study and the scope of malnutrition in the South African and the global context. They will be carefully trained on the study instruments that will be used such as FGDs and structured interview questions, administering of the intervention questionnaires and the measuring of height and weight in children and adolescents. Fieldworkers must be fluent in isiZulu and English. They will also be trained on their role in the study, as well as their interactions with members of the school, community and stakeholders such traditional leaders. Once the aims of the study and the fieldworker role is understood they will be given the information and consent forms in both English and isiZulu to role play as these have been selected as the two mediums of communication in the schools. During role play various scenarios will be created to allow fieldworkers to be adequately prepared in their approach to the schools in the study. Further training will be conducted with fieldworkers whereby they are introduced to the equipment that will be used for the study. Repeated training and a pilot phase will focus on achieving inter- and intra-rater reliability of measures.

